### **Data Analysis**

The baseline characteristics of the two groups will first be compared using the chi-square test for categorical variables and analysis of variance for continuous variables. An intention-to-treat analysis will be used by imputing all non-responses at follow-up by baseline values (i.e. assuming failure or no change after the intervention), to yield more conservative effect size estimates.

SPSS for Windows (SPSS version 26.0; IBM Corp., Armonk, NY, USA) will be used for the quantitative data analysis. Descriptive statistics will be used to calculate the mean, standard deviation, and frequency of the demographic and health-risk behaviour data. The primary analysis including the main effect, i.e., behavioural changes at 6 months in the intervention group versus those in the control group, will be performed using a chi-square test or Fisher's exact test. The secondary analyses will (1) assess the main effect adjusted for baseline differences, (2) assess the secondary outcomes (health-related quality of life) at 6 and 12 months, and (3) construct a generalised estimating equation model (GEE). The GEE model will be used to calculate the adjusted odds ratios for the self-reported the number of healthy lifestyles engaged in, after adjusting for the baseline demographic and clinical characteristics that show significant differences, and the within-subjects effect of the repeated-measure outcomes (6 and 12 months).

We will conduct a cost-effectiveness analysis (CEA) using standard methods. The CEA will be populated using empirical 12-month RCT data. An ingredients approach will be used to estimate the cost of the intervention programme, including that of the intervention material (e.g., leaflets and videos), the administration cost, and the time taken to deliver the intervention. The health effectiveness outcomes will include the number of participants who have adopted healthy lifestyles at 6 and 12 months and their QALYs.

We will use a qualitative approach to examine participants' experiences after receiving the general health promotion intervention based on self-determination theory. Based on the number of healthy lifestyles they adopt at 12 months, 20 participants from the intervention group (10 with a higher number of healthy lifestyles they adopt and 10 with a lower number) will be interviewed. The final sample size will depend on the data saturation. An in-depth, one-on-one, audiotaped, semi-structured interview will be conducted with each participant. The data analysis process will begin immediately after each individual interview, in accordance with the thematic analysis framework introduced by Braun and Clarke, using NVivo v12 (2018; QSR International Pty Ltd, Melbourne, Australia). The codes, categories, and themes generated through this process will be compared. HK\$200 supermarket coupon as an incentive to participants who have completed in-depth interview.

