#### Subjects

Chinese adults who attend one of the five EDs in various clusters in Hong Kong because of physical discomfort and if they meet the following criteria will be invited to participate. The inclusion criteria will be as follows: (1) being aged  $\geq 18$  years, (2) being triaged as semi-urgent (level 4) or non-urgent (level 5) and discharged home on the same day after receiving medical attention, (3) having at least one health risk behaviour (tobacco use, harmful alcohol consumption, unhealthy diet, and physical inactivity), and (4) owning a smartphone and having an ability to use instant messaging applications (e.g. WhatsApp or WeChat). The Exclusion criteria will be as follows: (1) having a poor cognitive state or mental illness and (2) being diagnosed with NCDs and undergoing regular follow-ups in outpatient clinics, and (3) participating in another related study.

The specific criteria for each health risk behaviour are listed in Appendix 1. People who do not have a smartphone or use WhatsApp/WeChat (unlikely in Hong Kong) will be provided brief advice and a Practical Resource Hub for Healthy Life leaflet on healthy lifestyles but will be excluded from the study.

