### **Sample size**

We used G\*Power to estimate the sample size based on the results of our pilot study conducted at an ED and a previous study using a brief smoking cessation intervention based on self-determination theory. The results of the pilot study showed an approximately 12% between-group difference in successfully adopting at least one healthy lifestyle at 6 months (the primary outcome of this proposed project). However, we opted for a more conservative effect size for our sample size calculation. Based on our previous large-scale RCT on a brief smoking cessation intervention based on self-determination theory, we expect a between-group difference of at least 5% ( $\geq 10\%$  in the intervention group vs.  $\leq 5\%$  in the control group) in the primary outcome at 6 months. To detect a significant between-group difference with a power of 80% at a significance level of 5% (two-tailed) in the proportion of participants modifying their health risk behaviours and/or adopting healthy lifestyles, 435 participants will be needed per group. To account for a potential attrition rate of 30% at the 6-month follow-up, we will recruit a total of 1,242 participants.

Based on the number of EDs visits (1.8 million) in Hong Kong between 2021 and 2022, we are confident that we will be able to recruit the required number of participants within 18 months.

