### **Data processing and analysis**

#### **Instruments:**

We will use available objective assessment tools to supplement the participants' self-reported outcomes to determine changes in their health-risk behaviours after the intervention. For verifying smoking cessation, we will use the biochemically validated 7-day point prevalence of abstinence, determined by a saliva cotinine level of  $<115$  ng/ml and an exhaled carbon monoxide level below  $<4$  ppm. Only those who meet both these criteria will be regarded as biochemically validated abstinent individuals; otherwise, the participants will be considered to have failed the validation. HK\$200 supermarket coupon being the incentive for completing biochemical validations

**A behavioural risk-factor questionnaire** will be used as the patient-report outcome measure to collect data on eligible participants' demographic and health-risk behaviours (tobacco use, binge drinking, unhealthy diet and physical inactivity) at baseline and at 3, 6, and 12 months. Moreover, participants' blood pressure and body mass index will be documented. This questionnaire was used to investigate multiple health-risk behaviours among Chinese adults in Hong Kong in 2021.

**The EuroQoL 5-Dimension 5-level (EQ-5D-5L)** will be used to assess the participants' health-related quality of life at baseline, 6 months, and 12 months. The psychometric properties of the Chinese version of the EQ-5D-5L were tested, and the findings indicate that this tool is a valid, reliable, and sensitive measure of health-related quality of life. A Chinese-specific EQ-5D-5L value set will enable the calculation of health utility scores applicable to the Chinese population and quality-adjusted life-years (QALYs) for conducting cost-effectiveness analysis.

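### Baseline carry-forward for every missed follow-up is conservative only if retention is about equal in both arms, and it is unsuitable for EQ-5D-5L because the baseline is the ED-visit score

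*Protocol*

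**What the plan says.** The Protocol, Data Analysis, sets one missing-data rule for the intention-to-treat analysis: "imputing all non-responses at follow-up by baseline values (i.e. assuming failure or no change after the intervention), to yield more conservative effect size estimates". The rule is not limited to the adoption outcome, and its no-change reading fits a continuous score, so as written it also covers EQ-5D-5L.

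EQ-5D-5L is used to assess "health-related quality of life at baseline, 6 months, and 12 months" (Instruments), and improvement in it at 6 and 12 months is a secondary outcome (Outcome measures). Baseline data are collected in the ED (Randomisation and allocation concealment; Recruitment), from people "who attend one of the five EDs in various clusters in Hong Kong because of physical discomfort" (Subjects).

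On missingness, the Sample size section gives only a "potential attrition rate of 30% at the 6-month follow-up". It is not split by arm, and there is no figure for 12 months.

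**The concern.** Under missing = failure, the expected observed adoption rate in an arm is its true rate multiplied by its retention. The between-arm contrast then mixes the treatment effect with any difference in retention. If retention is equal, the effect shrinks and the test keeps its level, so the stated rationale is correct. If it is not, the estimate moves towards the better-retained arm, and a difference can appear with no effect behind it. The Protocol states the benefit without the condition.

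A retention gap is plausible from the Protocol's own description. The intervention arm gets roughly weekly WhatsApp/WeChat messages tied to a chosen goal, videos and an invitation to ask questions. The control arm gets SMS messages with general advice.

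For EQ-5D-5L there is a second problem. The value carried forward was recorded on the day a person came to an ED unwell. Any recovery after the visit is set to zero for each non-responder, so the rule dilutes a true effect on change when retention is equal and biases the comparison when it is not.

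**Working it through.** **Inputs from the Protocol.** Adoption of 10% versus 5% at 6 months, 80% power, two-sided 5%, 30% attrition, 1:1 allocation, total 1,242, hence 621 per arm.

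**Assumptions (not in the Protocol).** Retention by arm, averaging 70%; within each arm, non-responders adopt or recover at the same rate as responders; an EQ-5D-5L recovery of 0.10 in both arms; an SD of change of 0.15 to 0.20.

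**The plan's own figures.** Pooled-variance formula for two proportions:

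n = [1.960·√(2·0.075·0.925) + 0.842·√(0.10·0.90 + 0.05·0.95)]² / 0.05² = 434.4, so 435 per group. This matches "435 participants will be needed per group". Then 870 / 0.70 = 1,242.9, against the stated 1,242. Both reproduce.

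**Adoption, equal retention.** 0.10 × 0.70 = 7.0% and 0.05 × 0.70 = 3.5%. The difference falls from 5 to 3.5 points, type I error is 5.0%, and power at 621 per arm is 79.0%. Here the rule is conservative as claimed.

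**Adoption, unequal retention, no true effect.** With true rate p in both arms, the expected difference is p × (r_I − r_C). The rejection probability is that of the pooled z (chi-square) test at 621 per arm. Example with p = 10% and 75/65 retention: 7.5% versus 6.5%, a spurious 1.0 point; null standard error √(2·0.07·0.93/621) = 0.0145; rejection 10.6%.

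| True adoption, both arms | 70/70 | 72.5/67.5 | 75/65 | 80/60 |
|---|---|---|---|---|
| 5% | 5.0% | 5.7% | 7.7% | 16.0% |
| 10% | 5.0% | 6.4% | 10.6% | 28.2% |
| 20% | 5.0% | 8.0% | 17.4% | 52.9% |
| 30% | 5.0% | 9.9% | 25.4% | 73.8% |

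**Adoption, planned effect present.** The expected estimate is 0.10·r_I − 0.05·r_C:

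- 75/65 retention: 7.50% − 3.25% = 4.25 points.
- 80/60: 8.0% − 3.0% = 5.0 points, so no shrinkage, and a risk ratio of 2.67 instead of 2.0.
- 65/75: 6.50% − 3.75% = 2.75 points.

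**EQ-5D-5L, how many are affected.** 0.30 × 1,242 = 372.6, about 373 participants (about 186 per arm), would carry their ED-visit score at 6 months.

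**EQ-5D-5L, size.** Let g be the recovery common to both arms and δ the true effect on change. After carry-forward the expected difference in mean change is

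r_I·(g + δ) − r_C·g = r_I·δ + (r_I − r_C)·g.

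- Equal 70% retention: 0.70·δ, a dilution to 70%.
- δ = 0, g = 0.10, 75/65: (0.75 − 0.65) × 0.10 = 0.010, from nothing.
- δ = 0, g = 0.10, 80/60: 0.020.

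Simulated two-sided t-tests (4,000 runs, 621 per arm, δ = 0, g = 0.10) reject in 26% of trials (SD 0.15) or 18% (SD 0.20) at 75/65, in 75% or 52% at 80/60, and in about 5% at 70/70.

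**The case against.** The strongest reply is that the rationale is right under the only attrition figure the Protocol gives. A single 30%, not split by arm, shrinks the planned effect and keeps the error rate. Even at 75/65 the planned 5 points are estimated as 4.25. A reader might infer that the rule is never conservative; the arithmetic does not support that. Missing = failure would also be exactly right if those lost had in fact all failed. This stands, and it is why the rule may remain the main analysis for adoption.

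The retention gap is assumed. Controls also get an AWARD-based telephone call, messages at a similar frequency and the same assessment schedule, so neither the size nor the direction of a gap is documented. A 5-point gap gives type I error of 5.7% to 9.9%. The highest error rates also need 20% to 30% adoption, above the planned 5% and 10%. This limits the size of the concern but does not remove the missing condition.

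Four further readings are tempting but not supported:

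- **Standard errors.** A reader might infer that single-value filling makes standard errors too small, or creates artificial within-person correlation in the GEE. In the cases checked with equal retention the tests kept about a 5% level, and nothing was calculated that shows a GEE problem. What is shown is bias from unequal retention, and dilution.
- **12 months.** A reader might carry the 30% over to 12 months. The Protocol gives it for 6 months only.
- **Severity at baseline.** Participants are triage level 4 or 5 and go home the same day. Some recovery is plausible, but the Protocol does not quantify it.
- **QALYs.** The cost-effectiveness paragraph mentions no imputation. QALYs inherit the problem only if they are built on the imputed scores.

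A statistical analysis plan may exist and contain sensitivity analyses, so their absence here is not counted as a fault. The point rests on a rule and a rationale that the Protocol itself states.

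**Conclusion.** The point holds in two parts.

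For adoption, the statement that the rule gives conservative estimates needs a condition that the Protocol does not state: about equal retention by arm. Without it, and with no true effect, an assumed 10-point gap raises type I error to 7.7% to 10.6% at 5% to 10% adoption and to about 25% at 30%, always in favour of the better-retained arm. These figures assume that non-responders adopt at the same rate as responders.

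For EQ-5D-5L the rule itself is unsuitable. It gives every non-responder an ED-visit score and no improvement. The consequence is dilution to about 70% under equal attrition, or a spurious 0.010 under 75/65 retention with an assumed recovery of 0.10. The direction follows from the documents if scores recover after the visit; the size depends on the assumed recovery and retention.

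This should be corrected, but it does not invalidate the design or the sample size.

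**What to change.** - **EQ-5D-5L:** do not apply baseline carry-forward. Analyse the 6- and 12-month scores with a mixed model on observed data, with the baseline score as a covariate.
- **QALYs:** state that missing utilities are handled by multiple imputation.
- **Adoption:** missing = failure may stay as the main analysis. Replace the unconditional claim of conservatism with the condition that retention is about equal, report attrition by arm, and add a sensitivity analysis by multiple imputation using the baseline and 3-month behaviours, which are already collected.

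The cost is wording and some programming; no new data are needed. The drawbacks are more modelling and reliance on missing at random for EQ-5D-5L. That assumption cannot be tested either, which is also why multiple imputation is proposed for adoption only as a sensitivity analysis: if people who fail tend to drop out, it would overstate adoption.

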Title:

A proactive approach to prevent non-communicable diseases through screening and educating emergency department attendees to adopt healthy lifestyles: A randomised clinical trial

Introduction:

Hong Kong is facing a growing burden of non-communicable diseases (NCDs), such as cardiovascular diseases, cancer, diabetes, and chronic respiratory diseases, exacerbated by an aging population. The World Health Organization has identified four major behavioural risk factors that substantially contribute to NCDs and can increase the risk of death: tobacco use, excessive alcohol consumption, an unhealthy diet, and physical inactivity. Most premature deaths from NCDs could have been prevented through lifestyle modifications.

In 2021, we conducted a large population survey (N = 5,737) in all 18 districts of Hong Kong to investigate the health-risk behaviours of Chinese adults. The results showed that 80.3% of the participants had at least one health-risk behaviour, and 47.0% of the participants had two or more health-risk behaviours. In response to the challenges posed by the increasing prevalence of NCDs, the government has committed to enhancing district-based primary healthcare services by establishing health centres in all districts across Hong Kong and launching the Chronic Disease Co-Care Pilot Scheme in 2023. However, many Chinese adults lack motivation or experience difficulty in adopting a healthy lifestyle, especially if they do not receive advice or support from healthcare professionals. In addition, the survey findings revealed that more than half of the participants had not undergone regular body check-ups or monitored their physical health at home in the past 3 years. Although regular body check-ups are crucial for preventing NCDs, a common misconception among many Chinese adults is that they do not need physical check-ups if they feel well. Thus **a proactive approach is required** to screen people with health-risk behaviours and help them adopt healthy lifestyles, including quitting smoking, avoiding excessive alcohol consumption, maintaining a balanced diet, and engaging in regular physical activity.

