### Randomisation and allocation concealment

To prevent the potential risk of treatment contamination within the ED, randomisation will not be performed there. Instead, the research assistant (RA) will input baseline data collected at the ED directly into the web-based trial entry form linked to a computerised database. Subsequently, randomisation will be performed at the principal investigator's institution by an independent statistician who will have no other involvement in the study. Stratified block randomisation with 1:1 allocation will be conducted using varying block sizes of 4–10 to achieve an appropriate balance of participant numbers between the intervention and control groups and to optimise allocation concealment.

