#### **Outcome measures:**

The **primary outcome** will be the number of healthy lifestyles adopted at 6 months. The criteria of successful adopting a healthy lifestyle are presented in Appendix 1.

**The secondary outcomes** will be the number of healthy lifestyles adopted at 12 months and improvement in health-related quality of life at 6 and 12 months.

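### Randomisation is stratified but the primary test is unadjusted: valid, at most slightly conservative, and improvable at no cost by pre-specified adjustment

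*Protocol*

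**What the plan says.** - **Design** (Protocol, Randomisation and allocation concealment): "Stratified block randomisation with 1:1 allocation will be conducted". The stratification factors are not named there. They may be recorded elsewhere, and their absence is not itself the point.
- **Primary analysis** (Protocol, Data Analysis): the between-group comparison of behavioural change at 6 months "will be performed using a chi-square test or Fisher's exact test".
- **Adjustment** (same section): one secondary analysis will "assess the main effect adjusted for baseline differences". The GEE model, also secondary, adjusts for those baseline characteristics found to differ significantly between the groups. Neither the strata nor the baseline number of risk behaviours is named as a covariate in any analysis.
- **Eligibility** (Protocol, Subjects): participants enter by "having at least one health risk behaviour (tobacco use, harmful alcohol consumption, unhealthy diet, and physical inactivity", so they start with one to four risk behaviours.
- **Outcome**: Outcome measures says that the primary outcome "will be the number of healthy lifestyles adopted at 6 months". Sample size instead treats it as binary: "successfully adopting at least one healthy lifestyle at 6 months (the primary outcome of this proposed project".

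**The concern.** When arms are balanced within strata that predict the outcome, the between-stratum variation cancels from the treatment comparison. An unstratified test still counts that variation in its standard error, so its true type I error falls below 5% and some power is lost. The number of risk behaviours at entry is a plausible predictor of the same kind, because someone with three has more openings for change than someone with one. The baseline questionnaire already records it.

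The adjustment that is planned does not fill the gap. Choosing covariates by baseline significance follows chance imbalance rather than prognosis, and it leaves the model unknown until the data are seen. At stake is some efficiency in the primary result, together with a primary analysis that follows the design.

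**Working it through.** **1. The plan's own figure.** Inputs from Sample size: 10% versus 5%, two-sided 5%, power 80%. With pooled variance and no continuity correction,

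n = [1.960·√(2·0.075·0.925) + 0.842·√(0.10·0.90 + 0.05·0.95)]² / 0.05² = (0.730 + 0.312)² / 0.0025 ≈ 434.4, so 435 per group.

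For attrition, 870/0.7 = 1,242.9, against the stated 1,242. Both figures reproduce, and they rest on the unadjusted comparison.

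**2. How prognostic is the baseline number?** The Introduction reports a survey in which "80.3% of the participants had at least one health-risk behaviour" and "47.0% of the participants had two or more health-risk behaviours". Among people with any risk behaviour, (80.3 − 47.0)/80.3 = 41.5% have exactly one and 47.0/80.3 = 58.5% have two or more. *Assume* that trial entrants resemble the survey, that each behaviour has the same independent chance q of success, and that the second group has exactly two. Then

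0.415·q + 0.585·[1 − (1 − q)²] = overall rate.

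- Overall 5%: q = 3.2% with one behaviour, 6.3% with two.
- Overall 10%: q = 6.5% with one behaviour, 12.5% with two.

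Both correspond to an odds ratio (OR) of about 2 between the two groups.

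**3. Unadjusted against stratified test.** Simulation, 100,000 replicates per scenario, arms balanced 1:1 within strata.

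- Chi-square: z = (a − b)/N ÷ √[2p̄(1 − p̄)/N], where a and b are the successes in the two arms, N is the number per arm and p̄ = (a + b)/2N.
- CMH: z = Σ(Xₛ − tₛ/2) ÷ √ΣVₛ, with Vₛ = mₛ²tₛ(2mₛ − tₛ)/[(2mₛ)²(2mₛ − 1)]. Here mₛ is the number per arm in stratum s, Xₛ the intervention successes and tₛ all successes.

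The stratum effects (ORs and site spread) are assumed, as are the rates and sample size in the last three rows.

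| Scenario | Control rates by stratum | Power, chi-square / CMH | Two-sided alpha, chi-square / CMH |
|---|---|---|---|
| 5% v 10%, 435 per arm, OR 1 | 5.0%, 5.0% | 81.2% / 81.2% | 0.049 / 0.049 |
| same, OR 2 | 3.2%, 6.3% | 81.3% / 81.4% | 0.049 / 0.049 |
| same, OR 4 | 1.9%, 7.2% | 81.3% / 81.6% | 0.047 / 0.049 |
| same, OR 8 | 1.0%, 7.8% | 81.5% / 82.2% | 0.046 / 0.050 |
| same, five equal sites, log-odds SD 0.6 | 1.9% to 9.5% | 81.1% / 81.4% | 0.047 / 0.050 |
| same, five equal sites, log-odds SD 1.0 | 0.8% to 12.5% | 81.7% / 82.8% | 0.045 / 0.050 |
| 30% v 36.5%, 870 per arm, OR 2 | 21.8%, 35.8% | 82.4% / 83.0% | 0.048 / 0.051 |
| same, OR 4 | 14.7%, 40.8% | 83.2% / 85.4% | 0.042 / 0.050 |
| same, OR 8 | 9.2%, 44.7% | 84.4% / 88.2% | 0.034 / 0.050 |

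The Monte Carlo standard error of each power figure is about √(0.81·0.19/100,000) = 0.12 point, so a gap of 0.1 is effectively nil.

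**4. Reading the table.** At the planned rates the gain is nil to 0.7 point for the baseline number, and about 1 point for site differences so strong that control rates range from under 1% to over 12%. A gain of 2 to 4 points needs assumed rates near 30% and an OR of 4 to 8. In no scenario is the unadjusted test anti-conservative.

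**The case against.** The strongest reply is that the planned test is valid and that almost nothing is lost at the trial's own rates. That stands: this is an improvement, not the correction of an error. The loss is also conditional. Because the protocol names no stratification factor, nobody can show that the strata predict the outcome. If the baseline number of risk behaviours is not a stratification factor, the unadjusted test keeps its nominal level overall and adjustment offers only a modest gain in precision.

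Several stronger readings are tempting, and the documents do not support them:

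- *Baseline number caps the outcome.* No section says that only behaviours at risk on entry count. Read literally, the success criteria in Appendix 1 can be met by someone never at risk, and Data Analysis also speaks of lifestyles engaged in. A cap could in any case bind only the count. Every participant has at least one risk behaviour, so all can succeed on the binary outcome.
- *Chance imbalance distorts the primary result.* Random imbalance is already covered by the error rate of the unadjusted test, and a secondary analysis adjusts for baseline differences.
- *Fisher's test takes power below 80%.* Exact power at 435 per arm is 77.1% for Fisher against 81.1% for chi-square. But the wording reads as the usual small-count fallback, and the smallest expected count is about 435 × 0.075 ≈ 33, so it should not be triggered.
- *No confidence interval is planned.* Naming a test does not exclude one, and this detail commonly sits in a statistical analysis plan, which is not at hand.

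The choice of primary test cannot be set aside in the same way, because the protocol itself fixes it.

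**Conclusion.** The point holds as a free improvement of small size. The primary analysis does not use the stratification that the design provides, and the secondary adjustment relies on significance-based covariate selection. Type I error is not inflated, and the planned 435 per group and 1,242 in total stand. The expected loss is at most about 1 power point at 5% versus 10%. It reaches about 2 to 4 points only if adoption is near 30% and the predictor is strong.

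These sizes rest on assumed stratum effects, on exact balance within strata and, for the baseline number, on the survey split of 41.5% to 58.5% applying to trial entrants. The higher-rate scenarios also use an assumed 870 per arm, which is more than the trial will recruit, so they illustrate rather than forecast.

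**What to change.** 1. Name the stratification factors.
2. Take the binary outcome used for the sample size, at least one healthy lifestyle adopted at 6 months, and make its primary analysis either a CMH risk difference with 95% confidence interval, stratified by the randomisation strata, or a logistic model with the strata and the baseline number of risk behaviours, reported as a standardised risk difference with 95% confidence interval. Choose one in advance.
3. Keep the unadjusted chi-square test as a supportive analysis.
4. In the secondary models, replace covariate selection by baseline significance with the same pre-specified covariates.

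The cost is wording only. The behaviours are already collected at baseline, and neither the data collection nor the sample size changes. The count and binary descriptions of the primary outcome also have to be reconciled, which is a separate matter; the fix assumes the binary one.

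### The secondary GEE models lifestyles 'engaged in' rather than 'adopted', leaves its odds ratio undefined, and does not secure adjustment for the baseline number of risk behaviours

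*Protocol*

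**What the plan says.** Protocol, Outcome measures: the primary outcome "will be the number of healthy lifestyles adopted at 6 months", and the first secondary outcome "will be the number of healthy lifestyles adopted at 12 months". Protocol, Sample size: the pilot difference is a proportion, "in successfully adopting at least one healthy lifestyle at 6 months", and the planned rates are 10% vs 5%.

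Protocol, Data Analysis: the primary comparison "will be performed using a chi-square test or Fisher's exact test". Three secondary analyses follow: the main effect adjusted for baseline differences, quality of life at 6 and 12 months, and a GEE. On the last, the text reads: "The GEE model will be used to calculate the adjusted odds ratios for the self-reported the number of healthy lifestyles engaged in". A rule for choosing covariates comes next in the same sentence: "after adjusting for the baseline demographic and clinical characteristics that show significant differences". The repeated outcomes are those at 6 and 12 months; baseline is not one of them. The section names no link or distribution and no cut-point for the number, and it does not list the baseline number of risk behaviours as a covariate. Missing follow-up values are replaced by baseline values, described as failure or no change.

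**The concern.** Three things in the GEE sentence do not fit together.

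- **Outcome.** The outcome section counts lifestyles *adopted*; the GEE counts lifestyles *engaged in*. Read literally, the second is current status. Eligibility needs only one of four risk behaviours, so a participant with one already engages in three healthy lifestyles before any contact, and a participant with four engages in none.
- **Effect measure.** A number from 0 to 4 yields an odds ratio only if it is dichotomised, treated as events out of trials, or modelled as ordinal. These are different odds ratios, and the sentence does not say which is meant.
- **Covariates.** On the current-status reading, the baseline count is the strongest predictor of the outcome, yet it is admitted only through a significance test.

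At stake is the only repeated-measures analysis of behaviour and the only model named for the 12-month behavioural outcome. That outcome is also part of the trial's hypothesis.

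**Working it through.** **1. The plan's own figure.** For 10% vs 5%, two-sided 5%, 80% power, with mean rate 0.075:

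n = [1.96·√(2·0.075·0.925) + 0.842·√(0.10·0.90 + 0.05·0.95)]² / 0.05² = 434.4, so 435 per group, as stated. For attrition, 435/0.70 = 621.4 per group, or 1,242.9 in total; the stated 1,242 is 2 × 621. The sample size reproduces, and it rests on a proportion.

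**2. How often the baseline count would enter.** Under 1:1 randomisation a given baseline variable differs at the 5% level in about 5% of trials. The protocol sets no threshold for this screening, so 5% is an assumption, as is that the count is among the variables screened and is not a stratification factor (none is named). The count would then be omitted about 95% of the time.

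**3. Baseline spread.** The Introduction's survey gives 80.3% with at least one and 47.0% with two or more risk behaviours. Among people with at least one:

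- two or more: 0.470/0.803 = 0.585; exactly one: 0.415.
- The SD of the baseline count is smallest if nobody has more than two: √(0.585·0.415) = 0.49.

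**4. Ceiling on power for the unadjusted current total.** Going from 5% to 10% adopting at least one lifestyle adds about 0.05 lifestyles per person. From baseline spread alone:

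| Per arm | SE = 0.493·√(2/n) | 0.05/SE | Power |
|---|---|---|---|
| 435 | 0.0334 | 1.50 | about 32% |
| 621 | 0.0280 | 1.79 | about 43% |

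Here 435 is the number needed with data; 621 is everyone recruited.

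**5. Simulated power.** The 58.5% was split over 2/3/4 behaviours as 100/0/0, 70/25/5 or 60/30/10 percent (assumed). Adoption rates per behaviour were solved to give 10% vs 5% adopting at least one. Nobody was assumed to lapse from a healthy behaviour. One time point was compared.

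| Analysis | 435 per arm | 621 per arm |
|---|---|---|
| 'Engaged in' total, unadjusted | 14–29% | 17–40% |
| 'Adopted at least one', or 'engaged in' adjusted for baseline count | 80–84% | 92–93% |

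**6. Lapse and validity.** A separate simulation at 435 per arm used four assumed sets of baseline prevalences.

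- With no lapse, the baseline-adjusted 'engaged in' count had 82–83% power. If 5% of healthy behaviours lapsed, it had 41–47%.
- The adopted count stayed at 80–83% throughout.
- With no true effect (one baseline scenario), both 'engaged in' analyses rejected in 4–6% of runs.

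**7. Imputation.** Carrying baseline forward gives 0 for an adopted count, which is failure. For a current total it gives anything from 0 to 3, so failure and no change are no longer the same thing.

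**The case against.** The strongest reply is that this is loose wording in a secondary analysis. The protocol elsewhere uses 'engaging in' for taking up a chosen lifestyle, the Data Analysis section describes the main effect as behavioural change, and equating failure with no change fits new adoption. Appendix 1 writes its success criteria as current states, so the ambiguity touches 'adopted' as well. All of this stands: the current-total reading is possible, not established, and the power figures depend on it.

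A reader might infer that an odds ratio is simply the wrong measure here. The documents do not support that. A binomial, events/trials or cumulative-logit GEE would each give a valid one, and naming the link could be left to an analysis plan. What remains is that the protocol itself pairs 'number' with 'odds ratios' without saying which contrast is meant.

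A reader might also infer that baseline differences bias the GEE, or that it would probably look null beside a positive primary result. Randomisation prevents the first, and the simulated error rates agree. The second would need the current-total reading, omission of the baseline count and the assumed spread all at once, and no GEE was fitted. Nor is the GEE the only adjusted analysis of behaviour, since the first secondary analysis also adjusts for baseline differences.

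The survey covers the general population, whereas the trial enrols emergency attendees and excludes people with NCDs under regular follow-up. It is therefore a proxy.

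**Conclusion.** The point holds as a mismatch to correct in a secondary analysis. The GEE outcome is worded differently from the defined outcome, the contrast behind its odds ratio is undefined, and the covariate rule would usually leave out the baseline number of risk behaviours. If 'engaged in' is the current total, the cost is precision: about 14–29% power at 435 per arm, or 17–40% at 621, against 80–84% or 92–93% for the alternatives. Those figures assume the survey distribution and splits above, 10% vs 5% adoption, no lapse and a single time point. If 'engaged in' was meant as 'adopted', this loss does not arise and only the wording and the covariate rule need attention. The primary chi-square or Fisher test and the sample size are unaffected on either reading.

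**What to change.** In Protocol, Data Analysis, replace the GEE sentence along these lines:

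*A GEE with binomial distribution and logit link will be fitted to whether the participant has adopted at least one lifestyle, by the Appendix 1 criteria, among the behaviours at risk at baseline. The model will include group, time (6 and 12 months), group-by-time and the baseline number of risk behaviours, the last irrespective of any baseline test. Odds ratios will be reported separately at 6 and 12 months.*

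Optionally add a supportive binomial events/trials GEE for the number adopted out of the number at risk at baseline, with the same terms. Its odds ratio is per behaviour at risk, not per person, and should be labelled so.

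The pre-specified covariate replaces the significance-based rule. Modelling adoption is preferable to keeping a current total and adjusting it, because the adjusted total loses power if healthy behaviours lapse. The cost is two or three sentences, settled before unblinding. No new data are needed, since the baseline questionnaire already gives the count.
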